| Phase:                                                  | not applicable                                                                                                                                                                                                                                                                                                                                                                                                                                                                                                                                                              |
| Description of Sites/Facilities Enrolling Participants: | 24 hospitals or health systems in the US, Canada, and Singapore                                                                                                                                                                                                                                                                                                                                                                                                                                                                                                             |
| Description of Study Intervention:                      | Participants will be randomized to receive open reduction and internal fixation with a volar locking plate, closed reduction and external fixation with a bridging external fixator device with or without supplemental k-wire fixation, or closed reduction and percutaneous pinning with k-wires. Participants in the observation arm will be treated with closed reduction and casting.                                                                                                                                                                                  |
| Study Duration:                                         | 92 months. April 2013-December 2019                                                                                                                                                                                                                                                                                                                                                                                                                                                                                                                                         |

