### Public Health Importance and Economic Burden

There are over 37 million individuals 65 years of age and older in the US, an increase of nearly 2 million over the past five years. This number will continue to rise as Baby Boomers age. Given that the incidence of DRF in the US population over the age of 65 is reported as 80 to 100 per 10,000, we extrapolate that nearly 372,000 individuals 65 years of age and over sustain this type of fracture every year.

The economic and social impact of this injury is substantial. The annual cost of treating DRFs in the elderly has been estimated from \$385 million to \$535 million. Added to these costs are the direct expenses of medical treatment, which include physician fees, facility fees, surgical equipment, and the cumulative costs of a structured rehabilitation program supervised by hand therapists. The non-monetary costs are great as well. While pain and disability related to DRFs is generally short-lived in younger patients, the impairment in the elderly can be long-lasting and greatly affect independent living. Elderly patients do not adapt to immobilization as well as younger patients. The prolonged

immobility renders the elderly to be dependent on others to complete everyday tasks and hampers their participation in social activities. Disability can last long after the immobilization period, as much as 18 months or longer after injury. Finally, the feeling that one is a burden to others can have a great emotional impact on elderly individuals.

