| To compare the trend of recovery for DRFs treated with VLPS with the other fixation techniques and to determine predictors of outcomes

To determine predictors of outcomes after surgical treatment of DRFs in the elderly | Michigan Hand Outcomes Questionnaire domain scores; SF-36; hand strength; wrist range of motion | MHQ domain scores allow closer inspection of specific areas of hand/wrist health; QOL and function affect outcomes and patient-reported satisfaction |
| Tertiary/Exploratory                                                                                                                                                                                                       |                                                                                                 |                                                                                                                                                      |
| To conduct a cost-utility analysis comparing the three treatment arms with the nonsurgical arm                                                                                                                                    | Medicare reimbursement; utility values derived from SF-36 scores                                | Most participants will be covered by Medicare; using SF-36 derived utility reduces participant burden of an additional utility questionnaire.        |

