Aim 5: To conduct a cost-utility analysis comparing the three treatment arms with the nonsurgical arm. To calculate QALYs for a cost-utility analysis, we have already begun development and initial testing of an online time trade-off (TTO) survey to determine utility for various health states related to DRF. Utility is the preference assigned to a particular health state on a scale where 0 represents death and 1 represents perfect health. Using the TTO method, a person is asked to choose how much time in his/her life he/she is willing to give up to be in a healthier state while avoiding a less healthy one. We will assess the utilities for different health states that could occur (malunion, nonunion, infection, etc) following DRF treatment. Data from the current study will be used to determine the outcomes and complications of DRFs. QALYs will then be calculated from the utilities, adjusted for years of life remaining for different age groups. We will also obtain utilities of elderly subjects from the community for a comprehensive analysis of the societal perspective, as recommended by the Panel on Cost Effectiveness in Health and Medicine. Medical costs will be assessed using the relevant charges/cost data for the procedures on all participants recruited at the Michigan Medicine. The costs of lost productivity will be valued as the average US hourly wage, as obtained from the US Bureau of Labor Statistics, of a person most likely to be affected by a DRF, multiplied by the average time to healing, as obtained from this study. Costs will be discounted at a rate of 3%. Sensitivity analyses will be done to change the assumptions to fit the extremes of these estimates. If, in changing these estimates, the results are similar, we can be assured of the stability of the conclusions. One- and two-way sensitivity analyses will be performed to determine the stability of the incremental cost-utility ratio, which will incorporate the cost and utility range of the study subjects' in the calculations

---

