### 10.1.6 DATA HANDLING AND RECORD KEEPING

#### 10.1.6.1 DATA COLLECTION AND MANAGEMENT RESPONSIBILITIES

#### 10.1.6.2 DATA COLLECTION FORMS

From each participant, data forms such as, Participant Demographic Questionnaire, RAPA, SF-36, MHQ, Hand Function Data form will be collected by the study coordinator at every visit. The surgeon will complete the Surgery Data form after surgery and complication checklist at every visit after surgery and these forms will also be collected by study coordinator.

The investigators will make every effort to preserve the study subjects' confidentiality. No one other than study personnel will have access to the study participants' records. Precautions will be taken to ensure that the records are in a locked cabinet. Records will not have the subjects' names listed on them, but instead an identification number will be assign to each subject, which only the investigators and study coordinators will be able to link to subject names. The subjects will also not be identified in any reports of this study.

To ensure compliance with the protocol, the Coordinating Center will create a MOP that is identical for each site. The MOP will be finalized after the study planning period. The MOP will contain instructions on how to complete all aspects of the study including randomization, measurements, data entry, and a copy of all study forms.

Data collection forms:

- Adverse Event Reporting form – Consists of the AE's with details pertaining to date of event, type of event, related or not, action taken and event outcome.
- Comorbidity Checklist – Questionnaire filled out by the participant at enrollment about their existing medical illness.
- Distal Radius Fracture Complication Checklist and Score Sheet- Form filled out by surgeon (PI) after surgery and every follow up visit, has information on complications developed such as nerve or bone/joint or tendon complications after surgery.
- General Health Questionnaire- information on general health in between follow up visits.
- Hand Edema Form – Measure of fingertip to palmar crease distance.
- Hand Function and Range of Motion data sheet- Measures grip, pinch and wrist range of motion of the injured arm and the normal arm.
- Hand Therapy Data Sheet – Information on type of therapy completed, number of visits, and when therapy was terminated.
- Inclusion/Exclusion Criteria – Includes fracture type and the detailed criteria for eligibility.

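### Aim 5 ties medical costs to the procedures at one of 24 sites, names no cost for hand therapy or treating complications, and contradicts the Medicare cost source in Section 3

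*Protocol*

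**What the plan says.** The Aim 5 text appears in Protocol Section 9.4.3 and again in 9.4.9. On medical costs it says: "Medical costs will be assessed using the relevant charges/cost data for the procedures on all participants recruited at the Michigan Medicine". It adds one further cost: "The costs of lost productivity will be valued as the average US hourly wage", multiplied by the average time to healing observed in the trial. It asks for community utilities to support a "comprehensive analysis of the societal perspective". Complications enter on the effect side: utilities are elicited for states such as malunion, nonunion and infection, and "Data from the current study will be used to determine the outcomes and complications of DRFs". One- and two-way sensitivity analyses are planned over the cost and utility range.

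Elsewhere the protocol says:

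- Section 1.1: the trial runs at "24 hospitals or health systems in the US, Canada, and Singapore".
- Section 2.2 (Public Health Importance and Economic Burden): the direct expenses of treatment include "the cumulative costs of a structured rehabilitation program supervised by hand therapists".
- Section 3: the endpoint entry for the same cost-utility objective is "Medicare reimbursement; utility values derived from SF-36 scores".
- Section 1.3: the Hand Therapy Data Form and the Complication Checklist are scheduled at every follow-up visit from 2 weeks to 24 months.
- Section 10.1.6.2: the therapy form holds "Information on type of therapy completed, number of visits, and when therapy was terminated".

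**The concern.** An incremental cost is only as complete as the resources it counts. The three operations and casting are expected to differ after the index procedure as well as in its price. The protocol's rationale is that they differ in immobilisation and complications, and Section 2.3.1 lists different complications for each operation. If medical cost stops at the procedure, any arm difference in therapy use or complication treatment drops out of the numerator of the cost-utility ratio. The same complications still lower the QALYs in the denominator, so they count as harm but not as expense.

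This bears directly on the Aim 5 hypothesis (Sections 4.1 and 9.1), which holds that volar plating costs more yet is dominant. If dominance means better outcomes at no greater total cost, later savings must offset the higher procedure price. Of the costs named, only lost productivity could supply that offset.

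There is also a plain conflict over where prices come from: one hospital's charge or cost data in Sections 9.4.3 and 9.4.9, Medicare reimbursement in Section 3. An analyst cannot follow both.

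**Working it through.** The protocol gives no cost figure, sample size or power for Aim 5, so there is nothing of its own to reproduce. The check sets the texts side by side and then scales the single-site source.

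**1. Which costs are named in Aim 5**

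| Item | Named as a cost in 9.4.3 / 9.4.9? | Recorded in the trial? |
|---|---|---|
| Index procedure | Yes, at one site | Surgery Data Form (10.1.6.2) |
| Lost productivity | Yes, wage × average time to healing | Time to healing taken from the trial |
| Hand therapy | No | Hand Therapy form, 2 weeks to 24 months |
| Treating complications | No (utilities only) | Complication Checklist, 2 weeks to 24 months; adverse event forms |
| Hardware removal, reoperation | No | No dedicated item described; only where the complication or adverse event forms capture it |

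**2. Direction of the error**

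For two arms, write Δ for the difference in mean cost.

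- Full incremental cost = Δprocedure + Δproductivity + Δtherapy + Δcomplications.
- Cost as written = Δprocedure + Δproductivity.
- Error = −(Δtherapy + Δcomplications).

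The error is zero only if the two omitted differences vanish or cancel. The protocol gives no therapy or complication prices and no expected use by arm, so neither sign nor size can be derived from it.

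**3. Source conflict**

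Section 3 names Medicare reimbursement. Sections 9.4.3 and 9.4.9 name charge or cost data from participants recruited at one institution. These are different price sources for the same aim. The utilities conflict in the same way: SF-36-derived in Section 3, a time trade-off survey in 9.4.3.

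**4. Scale of one site**

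Inputs: 474 randomised, 158 per surgical arm, 158 non-surgical (Section 9.2); 24 sites (Section 1.1).

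- Equal accrual (assumption): 474/24 = 19.75 randomised at one site; 19.75/3 = 6.6, about 7 per arm. Non-surgical: 158/24 = 6.6.
- Section 5.5 gives a goal of 36 randomised. Read as per site (assumption; the text does not say so): 36/3 = 12 per arm, and 36/474 = 7.6% of the randomised total.

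If mean costs were compared per patient, with equal SDs and a normal approximation, the 95% half-width in cost-SD units is 1.96 × √(2/n):

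- n = 6.58: 1.08 SD
- n = 12: 0.80 SD
- n = 158: 0.22 SD

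**The case against.** The best defence has four parts.

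**Scope.** A reader might infer that Aim 5 counts nothing but procedure charges, or that therapy and complication costs are expressly excluded. Neither is supported. Lost productivity is costed, so slower healing can carry a cost, and the text refers to cost data as well as charges. No item is excluded by name; the omission is inferred from a scope tied to the procedures. A detailed list of cost items may also belong in an analysis plan that is not shown. What remains is that the protocol does not leave scope open: it states a scope and a source, twice, and followed as written that scope does not reach therapy or complication treatment.

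**Precision.** A reader might infer that with about 7 per arm the cost difference is mostly noise. That is not shown. The half-widths assume a patient-level cost comparison at one site. The text can equally be read as a health-state model in which one site supplies prices and the whole trial supplies outcome and complication frequencies. They also rest on assumed accrual, and stating them as a share of mean cost would need a coefficient of variation that the protocol does not give.

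**Single site.** It might be said that the document as a whole uses one site's costs. Section 3 says otherwise. That answers the claim as a general statement, but only by exposing the contradiction. Medicare reimbursement is also a set of prices, not a list of resources, so it does not fill the scope gap.

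**Importance.** Hardware removal and tendon rupture are rated rare in Section 2.3.1, and Section 9.4.2 expects little repeat surgery. This stands and limits what those items could add. It does not bear on hand therapy. The planned sensitivity analyses vary the costs that are included; they do not bring in a category left out.

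**Conclusion.** The point holds in a bounded form. As written, Sections 9.4.3 and 9.4.9 limit medical cost to the procedures at one of 24 sites, with lost productivity added. No cost is named for hand therapy or complication treatment, despite the societal perspective and the protocol's own list of direct expenses. The price source contradicts Section 3.

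The consequence is a possible bias in incremental cost, of unknown sign and size, and prices drawn from a single institution. The figure of about 7 per arm applies only if costs are compared per patient at that site under equal accrual. The finding that therapy and complication costs are omitted rests on the stated scope, not on an explicit exclusion. Aim 5 is tertiary/exploratory in Section 3, so no efficacy or safety conclusion depends on this. It should still be corrected before the economic analysis is run.

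**What to change.** 1. Reconcile Sections 9.4.3 and 9.4.9 with the Section 3 endpoint table, so that one primary cost source is named. Settle the utility source in the same edit.
2. Define medical cost for participants at all sites, to 24 months, as the sum of: the index procedure; hand-therapy visits from the Hand Therapy Data Form; and treatment of recorded complications from the Complication Checklist and adverse event forms, including reoperation or hardware removal where those forms record it. Price each item at Medicare reimbursement, which Section 3 already names. Keep lost productivity as a separate component.
3. Retain the single-site charge or cost data as a sensitivity analysis.

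The cost is revised wording and a unit-price table; the therapy and complication forms are already scheduled. The downside is that some resource use would come from study forms rather than billing records, and rare items without a dedicated field may be incompletely captured. The report should say so.

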## 9.2 SAMPLE SIZE DETERMINATION

We propose to randomize 474 patients to one of three surgical arms (158 per surgical arm). We will follow another 158 non-surgical patients meeting the inclusion/exclusion criteria. Sample size was determined to have adequate power for Aim 1 based on the primary outcome of the MHQ summary score at 12-month follow-up. **We expect to have complete data for 12-month follow-up time from 126 patients in each group, after accounting for a conservatively estimated 20% decrease in sample size from losses to follow-up.** For Aim 1, we expect 126 patients per group to give 80% power to detect an 8 point difference in the mean MHQ summary scores between VLPS and CRP and between VLPS and EFP using a mixed-effects model with a two-sided 0.025  $\alpha$ -level test. This assumes a standard deviation (SD) of 18 points (corresponding to an effect size of 0.44 SD), an average of 24 patients per site and an intra-site correlation coefficient (ICC) of 0.012. **To adjust for potential within surgeon correlation, we will also consider either a three level hierarchical model with surgeons nested within site, or use surgeons instead of sites as random intercepts. If technical variation is mostly between surgeons, addressing within surgeon correlation will reduce the ICC, which would give larger power to detect the same effect size. Covariate adjustments will likely give greater power by reducing the variability when the covariates are associated with the outcome and are not highly correlated with other covariates in the model.** We expect the 8 point difference in MHQ score at 12-months as a minimally detectable and meaningful difference between VLPS and either CRP or EFP. Our retrospective study of patients treated with VLPS showed mean ( $\pm$ SD) MHQ scores of 77 ( $\pm$ 15) at 3 months, 81 ( $\pm$ 17) at 6 months, and 85 ( $\pm$ 18) at 12 months for elderly patients. We believe the observed improvement of 8 points from 3 to 12 months to be similar to the expected post-surgical improvement difference between VLPS surgery compared with either EFP or CRP.

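### Exploratory Aim 5 infers stability of the cost-utility ratio from one- and two-way changes over the range of individual subjects, which does not measure sampling uncertainty

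*Protocol*

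**What the plan says.** Aim 5 is a cost-utility analysis of the three surgical arms and the nonsurgical cohort, listed as tertiary/exploratory in section 3 of the Protocol. Section 9.4.3, repeated in 9.4.9, sets it out as follows.

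- Clinical inputs come from the trial: "Data from the current study will be used to determine the outcomes and complications of DRFs". Utilities for health states come from a time trade-off survey and are combined with remaining life-years to give QALYs.
- Costs come from one centre: "Medical costs will be assessed using the relevant charges/cost data for the procedures on all participants recruited at the Michigan Medicine".
- After the wage, healing-time and discounting inputs, the text says: "Sensitivity analyses will be done to change the assumptions to fit the extremes of these estimates". It then concludes: "If, in changing these estimates, the results are similar, we can be assured of the stability of the conclusions".
- A further sentence plans deterministic analyses, changing one or two inputs at a time, and names as their object: "the incremental cost-utility ratio, which will incorporate the cost and utility range of the study subjects' in the calculations".

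No interval, bootstrap or probabilistic analysis of cost, QALYs or their ratio is stated in the Protocol. Aim 1 (9.4.2), in contrast, reports 95% confidence intervals.

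Section 3 gives different sources for the same aim: Medicare reimbursement for cost, and SF-36 scores for utility.

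**The concern.** Complication rates, time to healing and costs are estimates from samples of patients, so an incremental cost or QALY difference between arms carries sampling error. The subject range does not represent that error. It reflects how far individual patients differ, and it widens as more patients are enrolled, while the error of a mean shrinks. Changing one or two inputs at a time also leaves out the joint sampling error of incremental cost and incremental QALYs, which matters most when the QALY difference, the denominator of the ratio, is near zero.

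At stake is how a cost-utility conclusion would be worded. Section 4.1 hypothesises that volar plating will be the dominant strategy. Under the stated text, that conclusion could be called assured, or be doubted, with no interval or probability attached.

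**Working it through.** **Figures to reproduce.** Aim 5 states no sample size, interval or ratio. The 126 per group used below is the section 9.2 figure: "We expect to have complete data for 12-month follow-up time from 126 patients in each group". It reproduces. For 8 points, SD 18, two-sided 0.025 and 80% power, n = 2 × (2.241 + 0.842)² × (18/8)² = 96.2, so 97. The design effect is 1 + 23 × 0.012 = 1.276, and 97 × 1.276 = 123.8, so 124 against 126 stated. Also 158 × 0.80 = 126.4. That count is of patients with 12-month data for the hand questionnaire. It is borrowed here only as an illustrative arm size.

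**Range against uncertainty of a mean** (assumes roughly normal values)

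- Expected half-range of 126 individuals, by simulation: 2.59 SD.
- 95% half-width of an arm mean: 1.96/√126 = 0.175 SD. Ratio 2.59/0.175 = 14.8.
- 95% half-width of a difference between two arms: 1.96 × √(2/126) = 0.247 SD. Ratio 2.59/0.247 = 10.5.
- At 1,000 per arm, the simulated ratio for a mean is about 52. More data make the mismatch worse.

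**What such a check would show.** The Protocol gives no threshold for similar results, so these simulations read it as the sign of the difference being unchanged. That reading is an assumption.

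1. Each arm mean is moved over its own subjects' range, 126 per arm:

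| True difference | Sign unchanged, full range or 5th–95th percentile | 95% interval excludes zero |
|---|---|---|
| 0 | 0% | about 5% |
| 0.2 SD | 0% | about 35% |
| 0.44 SD | 0% | about 94% |
| 1.0 SD | 0% | about 100% |

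Over the interquartile range, the sign is unchanged in about 3% of trials at 0.44 SD and 98% at 1.0 SD, so the answer depends on which range is chosen.

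2. Only a utility decrement common to both arms is varied, and the true complication rates are equal (assumed 10–30%). The QALY difference is then the decrement times the difference in observed rates, so no positive decrement can change its sign. The result looks stable in 92–94% of trials, although there is no true difference. A 95% test flags about 5%.

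The same kind of check can therefore point either way, depending on which inputs are moved.

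**Costs from one centre.** With equal accrual over 24 sites (assumed), 474/24/3 = 6.6 randomized patients per arm. The 95% half-width of a cost difference, as a share of mean cost, is 1.96 × CV × √(2/6.6): 32%, 54% or 108% for an assumed CV of 0.3, 0.5 or 1.0. If the goal of 36 randomized patients in section 5.5 is read as a per-site figure, there are 12 per arm, giving 24%, 40% or 80%. None of this error enters the stated analyses.

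**The case against.** The strongest reply is that one- and two-way analysis is a legitimate part of an economic evaluation, that it tests robustness to assumptions, and that a probabilistic analysis is commonly left to a SAP, which is not at hand. Much of this stands. The absence of a bootstrap from the Protocol is not itself the finding, and it cannot be said that none is planned. What remains is stated text: a method that uses the spread of individuals, and a sentence that draws assurance from similar results. Adding an analysis elsewhere would not correct that sentence.

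Three stronger readings are tempting, and the documents do not support them.

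- A reader might infer that the extremes are the subject range. The text does not link them. The extremes and the assurance come first, directly after the wage, healing-time and discount inputs; the subject range appears afterwards, in the sentence on one- and two-way analyses. The extremes are undefined and could mean confidence limits.
- A reader might infer a known risk of reporting the wrong sign. For 126 patient-level QALYs per arm, an assumed SD of 0.12–0.30 and a true gain of 0.02, that probability is 9–30% (25–40% for a gain of 0.01). The SDs and gains have no source in the Protocol, which describes survey utilities combined with trial outcomes, not two samples of 126 QALYs. These figures illustrate a different analysis.
- A reader might infer that the plan claims to separate a real ratio from chance. It claims only stability.

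**Conclusion.** The point holds as a minor one. The range of study subjects is the wrong measure of uncertainty for an arm mean. It is about 15 times too wide at an illustrative 126 per arm under normality. The stated analyses also omit the joint sampling error of incremental cost and QALYs. Similar results could therefore support robustness to the assumptions that were varied, but not assurance about the conclusions generally. The factor of 15 rests on normality and a borrowed arm size; the simulations rest on an assumed meaning of similar; the cost half-widths rest on assumed CVs and accrual. The direction of any error in the trial's actual result cannot be stated. The primary endpoint, the sample size and the randomized comparison on the hand questionnaire are untouched.

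**What to change.** 1. Reconcile the cost and utility sources in section 3 with those in 9.4.3 and 9.4.9. Until then, neither a range nor an interval is defined.
2. Add a probabilistic sensitivity analysis that draws trial outcome and complication rates, utilities and costs each from its own sampling distribution. Resample participant-level pairs only where both cost and QALY exist; with costs from one of 24 sites, a paired bootstrap across all sites cannot be run.
3. For the nonsurgical comparison, use the Aim 4 propensity adjustment and re-estimate it in each replicate. That cohort chose its treatment, and resampling alone would give a narrow interval around a confounded difference.
4. Report 95% intervals for incremental cost, incremental QALYs and net monetary benefit, with an acceptability curve.
5. Keep one- and two-way analyses for structural inputs such as the discount rate and wage. Where an estimated mean is varied, use its 95% interval, not the subject range.
6. In both sections, delete the assurance sentence or limit it to robustness against the assumptions varied.

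The cost is revised wording and some extra programming. The intervals may prove wide, particularly for cost, but that would be a fair account of what the data can show.
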